## Abstract

**Background:**

Relapse, often precipitated by drug-associated cues that evoke craving, is a key problem in the treatment of methamphetamine use disorder (MUD). Drug-associated memories play a major role in the maintenance of relapse. Extinction training is a common method for decreasing drug craving by suppressing drug-associated memories. However, the effects are often not permanent, which is evident in form of spontaneous recovery or renewal of cue-elicited responses. Based on memory reconsolidation theory, the retrieval-extinction (R-E) paradigm may be more effective in decreasing spontaneous recovery or renewal responses than extinction. After the original memory reactivated to a labile state, extinction will be introduced within the reconsolidation window, thereby updating drug-associated memories. However, there are still some controversial results, which suggest that the reactivation of drug-associated memories and the 10 min-6 h of limited time window are two main elements in the R-E protocol. Virtual reality (VR) is supposed to promote memory reactivation by providing vivid drug-related stimuli when compared with movies.

**Objective:**

The aim of this study is to examine the effectiveness of R-E training combined with VR on reducing spontaneous recovery or renewal of cue-elicited responses, in comparison to extinction, R-E training provided outside the time window of 6 h and R-E training retrieved using videos, in methamphetamine abusers.

**Methods:**

The study is a parallel matched controlled study including 95 participants with MUD. Participants will be randomly assigned to either a R-10 min-E group (methamphetamine-related cues retrieval in VR followed by extinction after 10 min) or a NR-10 min-E group (neutral cues retrieval in VR followed by extinction after 10 min) or a R-6 h-E group (methamphetamine-related cues retrieval in VR followed by extinction after 6 h) or a RV-10 min-E group (methamphetamine-related cues retrieval in videos followed by extinction after 10 min). Cue-evoked craving and reactivity will be assessed at pre-test and at 1 day, 1 week, 1 month, and 6-month post-tests.

**Discussion:**

To our knowledge, this study will probably be the first study to examine the efficacy of R-E training combined with VR to reduce cue-evoked responses in people with MUD. This innovative non-pharmacological intervention targeting drug-associated memories may provide significant clinical implications for reducing relapse, providing the study confirms its efficacy.

**Clinical Trial Registration:**

The trial is registered with Chinese Clinical Trial Registry at 17 October 2018, number: ChiCTR1800018899, URL: http://www.chictr.org.cn/showproj.aspx?proj=30854

## Introduction

Methamphetamine is the commonly abused illegal drug recent years in China and entails great personal and societal costs (1, 2). Even after long periods of abstinence from drugs, the risk of relapse remains high in people with methamphetamine use disorder (MUD) (3, 4). Relapse is a core characteristic of substance use disorders (SUDs) and a major obstacle to successful treatment. Craving or cue reactivity elicited by drug-associated stimuli is invoked as a main motivating force behind relapse (5, 6). As drug-paired stimuli (cues, contexts, and behaviors) that are repeatedly associated with the reinforcing properties of drugs over the course of drug use, when subsequently encountered, are known to evoke craving or cue reactivity and then result in compulsive drug taking (5–7). Drug-associated memories supposed to be a primary trigger of drug craving and relapse. This suggests that effective treatments focused on the manipulations of the cue-drug memory to reduce cue-elicited craving or reactivity are needed for relapse prevention of MUD.

Extinction training is a common method used to decrease craving and reactivity evoked by drug-associated stimuli in an effort to reduce relapse propensity through suppressing the cue-drug memory (8). Initially, it had been assumed that repeated, unreinforced presentation of drug-associated stimuli (without drug administration), would “extinguish” cue-elicited craving and reactivity. Extinction training has been applied in a variety of forms to treat SUDs in clinical studies with varying levels of success (9). However, these cue-evoked responses frequently reemerge after the passage of time (spontaneous recovery) or in the presence of drug-associated stimuli different from the ones used in extinction training (renewal) (10, 11). This suggests that extinction might involve a new “cue-no drug” learning to inhibit or interfere with the initial “cue-drug” association instead of erasing the original memory trace (12, 13).

Recent studies have proposed that retrieval-extinction (R-E) training, based on the theory of memory reconsolidation, may be more effective in reducing spontaneous recovery or renewal of cue-elicited responses than extinction through modifying drug-associated memories (14, 15). Memory reconsolidation is a process to maintain and strengthen consolidated memories over time, during which previously consolidated memories re-stabilize after it is retrieved or “reactivated” (16). The R-E training follows the rationale to reactivate original drug-associated memories to a labile state by a brief and/or weak exposure to the drug-associated stimuli, and then extinction training will be used to interrupt the reconsolidation process of drug-associated memories within a limited time window by incorporating new information, thereby updating the original drug-associated memories (16). The 10 min-6 h of reconsolidation window has been examined in preclinical studies (17, 18) without enough clinical studies in SUDs. To our knowledge, only two translational studies have used R-E training to treat SUDs, which found that R-E training in 10 min-6 h, had better intervention effects on inhibiting spontaneous recovery (19) or renewal (20) of cue-elicited responses than extinction training. Nonetheless, other studies failed to replicate the results (21, 22). One of the key reasons is that the consolidated memories had not been reactivated to a labile state (23) for memory reconsolidation.

Virtual reality (VR), which has high ecological validity, may improve the effects of R-E training from a methodological perspective. VR can provide a variety of vivid drug-associated cues and contexts for individuals to interact with and the individuals with SUDs will be immersed in customized scenes by putting on a headset. Previous studies found that using VR to present drug-associated stimuli and interact with these stimuli during the retrieval process evoke craving more robustly than using traditional methods, such as pictures (24) and videos (25, 26). It suggests that VR may be a promising way to reactivate drug-associated memories by providing vivid drug-associated stimuli (25). Thus, combined VR with R-E training may be a prospective approach to treat MUD.

The primary objective of the present study is to examine the effectiveness of R-E training combined with VR in decreasing cue-elicited craving and reactivity in individuals with MUD, when compared to extinction training or R-E training provided outside the time window of 6 h. The second objective is to examine the effects of VR in promoting the reactivation of drug-associated memories during R-E training. The R-E training combined with VR will be compared with the R-E training combined with videos during the retrieval in decreasing cue-elicited responses. The third objective is to examine the effectiveness of R-E training combined with VR in attenuating spontaneous recovery and renewal of cue-elicited responses when compared to the other three interventions. All the cue-evoked craving and reactivity will be assessed at pre-test and 1 day, 1 week, 1 month, and 6-month posttests after intervention to investigate how long the effectiveness of R-E training will last. A novel methamphetamine-related scene will be added to the follow-up post-tests to assess if the effectiveness can translate to the new drug cue-induced craving and reactivity.

## Materials and Methods

### Design

The study will be a randomized controlled comparative clinical trial with two successive days of therapy and 6 months of follow-up. It will involve four parallel groups, namely a R-10 min-E group (methamphetamine-related cues retrieval in VR group), a NR-10 min-E group (neutral cues retrieval in VR group), a R-6 h-E group (group that will receive extinction training outside the reconsolidation window of 6 h) and a RV-10 min-E group (methamphetamine-related cues retrieval in videos group).

### Participants

This study will be conducted at the Changsha drug rehabilitation center, Changsha, Hunan, and Women' drug rehabilitation Center of Guangdong province, Foshan, Guangdong. The inclusion criteria are as follows: 1) age: 18–45 years old; 2) a history of using methamphetamine meets Diagnostic and Statistical Manual of Mental Disorders Fifth Edition (DSM-5) criteria for MUD (27); 3) abstinence periods at least 2 weeks without obvious withdrawal symptoms (e.g., drowsiness and dysphoria); 4) able to speak and read Chinese; 5) a signed consent form; and 6) cue-elicited responses including self-report craving, heart rate, skin conductance responses, and electroencephalogram power spectrum are all more obvious in methamphetamine-associated scenes than in neutral scenes in VR during the pre-test (28).

The exclusion criteria are as follows: 1) a history of using illicit drugs other than methamphetamine or methamphetamine tablets (e.g., heroin, cocaine, marijuana); 2) uncontrolled medical illnesses or psychosis; 3) use of any medication or medical condition that may affect cardiovascular function and mental state; 4) some kinds of nervous system diseases may influence performing the experiment (e.g., epilepsy, parkinsonism); 5) a history of head trauma that caused a coma lasting more than 30 min; 6) movement disorders; 7) hearing impairments; 8) color blindness or color amblyopia; 9) a vision or corrected visual acuity less than 1.0. The subjects with psychiatric comorbidities and other kinds of SUDs will be excluded using DSM-5 (27, 29).

### Study Procedure

Psychotherapists in the rehabilitation center will make the advertisements and announcement for recruitment. The participants will be screened by a psychologist for eligibility. Then, the researcher will meet the eligible participants, describe the study procedure, discuss with the participants on the questions they concerned, and ask each eligible participant for informed consent.

Firstly, participants will attend a 1 h individual face-to-face interview to collect demographic information, the use history (dosage, duration, frequency) of methamphetamine, cigarettes, and alcohol and the questionnaire on anxiety. The use history of methamphetamine, cigarettes, and alcohol and the anxiety index will be regarded as variables for the data analysis. Then, a VR using practice with a neutral scene lasting 6 min for accommodation will be implemented. Participants will adapt to VR scenes and know how to operate wireless controllers of the VR system. After this, participants will attend a VR cue reactivity assessment as a pre-test, during which participants will engage in two VR sessions (composed of a methamphetamine-VR scene for 3 min and a placebo-VR scene for 3 min) with a real-time recording of psychophysiological reactivity (heart rate, skin conductance reactivity, and electroencephalic response). There will be a 1 min break between the two sessions, and the placebo-VR scene will always be presented before the methamphetamine-VR scene to avoid the disturbance elicited by the methamphetamine-related cues. Self-report craving to methamphetamine-related cues will be rated after exploring both VR scenes. The pre-test will be used not only for measuring the baseline of cue-elicited responses but also for screening the participants who will respond more robustly to methamphetamine-associated cues in VR. According to the inclusion criterion, participants the cue-elicited responses including self-report craving, heart rate, skin conductance responses, and electroencephalogram power spectrum are all more obvious in methamphetamine-associated scenes than in neutral scenes during the pre-test will be included in groups (28).

Thereafter, participants will be randomly assigned to one of four therapeutic groups using a randomization table generated by a sequence generator in a computer for matching. One group (R-10 min-E group) will receive R-E training, namely memory retrieval of methamphetamine-related cues in VR followed by extinction training after 10 min. Another group (NR-10 min-E group) will receive extinction intervention, namely memory retrieval of neutral cues in VR followed by extinction training after 10 min. The other group (R-6 h-E group) will receive R-E training outside the time window of 6 h, namely memory retrieval of methamphetamine-related cues in VR followed by extinction training after 6 h. The RV-10 min-E group will receive memory retrieval of methamphetamine-related cues in videos followed by extinction training after 10 min. Psychophysiological reactivity will be recorded instantaneously during the two times of intervention. The cue-elicited responses during the retrieval session will be assessed to indicate memory reactivation (28).

With the purpose of examining the effectiveness of R-E training in decreasing the spontaneous recovery of cue evoked responses, self-report craving and the VR cue reactivity assessment will be conducted at five different time points: pre-test, 1 day, 1 week, 1 month, and 6 months after the last intervention session. To measure the renewal effect, a new VR session with novel methamphetamine-related cues will be added to the VR cue reactivity assessment during the four post-tests compared to pre-test. Three psychotherapists with VR operation knowledge will conduct all the procedures for the four groups. The whole procedure of this study is depicted in a flow chart (**Figure 1**).

**Figure 1 f1:**
[figure not shown]
Flow chart of the study. STAI, State and Trait Anxiety Inventory; MA cues, Methamphetamine-related cues.

### Intervention

All four groups will receive two intervention sessions over two consecutive days (19, 20). The intervention process will be conducted by one of three psychotherapists including a 3 min memory retrieval session and a 30 min extinction training session. Psychotherapists should have technical ability to operate VR (self-developed through the collaborative work of the psychotherapists and researchers) to ensure the treatment's consistency and fidelity. The content of the extinction training session will be the same for the four groups. However, the intervention processes of four groups will differ in the content of the memory retrieval session and the time point of implementing extinction training.

#### R-10 min-E Group

Participants will receive two intervention sessions for the same, which both consist of memory retrieval for 3 min and extinction training for 30 min. The extinction training session will be implemented 10 min after the memory retrieval session. During the retrieval session, participants will be guided to explore a VR scene, which is considered as a high-risk situation for relapse, with both distal and proximal methamphetamine-related cues (e.g., a substance that appears to be methamphetamine, the water filter bottle of methamphetamine, straws, foil paper). In this way, the methamphetamine-associated memories of participants may be reactivated to a labile state.

During the extinction training session, six VR scenes with different methamphetamine-related cues in a room will be given to participants in six consecutive sessions. Participants will be asked to sit in front of a table on a sofa (or on a chair) in VR scenes. All the while, they will sit on a real sofa (or on a real chair) in the experimental environment in reality. Each VR session with one VR scene will last for 5 min. Six VR scenes will be presented in a randomized order to regulate individual differences in the relevance of craving-specific among participants. During the first and last minute of each VR session, participants will be instructed to observe the entire VR scene, and in the middle three minutes, a task for fully exposing methamphetamine-related cues will be assigned to the participants. After each session, participants are going to rate their craving to methamphetamine-related cues using a visual analog scale. Throughout the intervention process, psychophysiological cue reactivity will be recorded in real time.

#### NR-10 min-E Group

Participants will be provided with two intervention sessions for two days, both including 3 min of neutral cues retrieval followed by 30 min of extinction training 10 min after. The implementation of the retrieval session will guide participants to explore a neutral VR scene without methamphetamine-related cues. To ensure that the methamphetamine-associated memories of the participants will not be reactivated to a labile state, this session should be irrelevant to drug-associated stimuli.

The content of the extinction training session that the NR-10 min-E group will be exposed to is the same as the content that the other three groups will be exposed to.

#### R-6 h-E Group

Participants will receive two intervention sessions that the content of the retrieval session and the extinction training session will be identical to the R-10 min-E group. The only difference is that extinction training will be conducted 6 h after memory retrieval, when methamphetamine-associated memories are supposed to be reconsolidated again.

#### RV-10 min-E Group

Participants will receive two intervention sessions for two successive days. The duration and the time interval to implement the intervention sessions of the RV-10 min-E group are the same with the R-10 min-E group and the NR-10 min-E group. However, the method to present methamphetamine-associated cues of the RV-10 min-E group in the retrieval session is different from the other three groups. The participants will watch a video related to methamphetamine lasts 3 min to retrieve drug-associated memories. 10 min after the retrieval session, a same extinction training session will be implemented.

### Apparatus

The experiment is going to use HTC VIVE virtual reality system containing a headset (110 degrees, 1080×1200, 90Hz), two wireless controllers, and two base stations. Through the head tracker, participants can visually explore the VR scenes and walk around freely in a 3.0 m× 4.0 m space. The head orientation of participants will define the direction of locomotion. The wireless controllers will be used to interact with VR scenes and to provide their ratings on the visual analog scales. The VR scenes will be generated and run on a desk computer (Alienware 15-R2748, i7-7700HQ 16G 256GSSD+1T GTX1070 8G discrete graphics FHD). The required software is Microsoft Windows 10 (64-bit edition). The heart rate and skin conductance reactivity will be recorded by Biopac 16 Physiological multichannel instrument (BIOPAC MP150) including two transmitters and a signal projector connecting to a laptop. The electro encephalic response monitor has been developed by XinSi company in Beijing, China. The monitor has proven to be effective in recording electroencephalic responses (30).

### VR Scenes and Videos

The main software exploited to create the VR scenes is unity 3D. Unity is an ultimate and available game development platform used to build and deploy high-quality 3D games across VR. The neutral scene in the process of VR using practice will be a room with a desk, two spheres, two cubes, and a visual analogue scale. In a previous investigation of 60 people with MUD, four completely different VR scenes were constructed by unity 3D, two of which contexts were related to methamphetamine, while the other two were neutral contexts with neutral goods rather than methamphetamine-related cues. Two methamphetamine-related scenes are a living room and a bedroom with methamphetamine-related cues on a table or desk. To resemble the most familiar methamphetamine-related environment of participants in real life, a suitable VR scene will be chosen for each participant from the two methamphetamine-related rooms to be implemented in the pre-test, the memory retrieval session, and four post-tests (31). The other one of the two methamphetamine-related rooms which has not been chosen in the pre-test will be presented in four post-tests as a novel scene to test the renewal effect. Six methamphetamine-related scenes in the extinction training session are based on these two rooms with a double or a triple number of methamphetamine-related cues in different places of the rooms. One of the two neutral VR scenes has been prepared for the memory retrieval session that the NR-10 min-E group will view. The other one will be implemented in cue reactivity assessments as a baseline for the pre-test and post-tests to compare with methamphetamine-related VR scenes.

The dynamic VR scenes also provide participants with direct, realistic interactions, such as the grabbing of objects and physical or mechanical reactions to the user's presence. The four VR scenes including two methamphetamine-related scenes and two neutral scenes will be validated by a small number of people with MUD (n = 10) using self-report craving. All the VR scenes will be run in the software named Steam, which is a game platform as well.

The methamphetamine-associated video used in the retrieval session of the RV-10 min-E group will include an actress using *in vivo* mock methamphetamine paraphernalia (e.g. glass pipe, mock syringe, medical tubing, and a small plastic bag containing a substance that appears to be methamphetamine) to make a water filter bottle for administrating methamphetamine. The video will be validated by the same group of people with MUD (n = 10) using self-report craving. The video will be run on the desk computer.

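### On the natural reading, the 'novel' room for the renewal test is also an extinction room, so the test measures generalisation and not renewal as the protocol defines it

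*Protocol article*

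**What the plan says.** The Introduction explains that extinguished responses can return "in the presence of drug-associated stimuli different from the ones used in extinction training (renewal"). The criterion is therefore difference from the extinction stimuli.

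The VR Scenes and Videos section lists the available material: "Two methamphetamine-related scenes are a living room and a bedroom with methamphetamine-related cues on a table or desk". From these, "a suitable VR scene will be chosen for each participant from the two methamphetamine-related rooms" for use at pre-test, at retrieval and at the four post-tests. The room "which has not been chosen in the pre-test will be presented in four post-tests as a novel scene to test the renewal effect". The next sentence reads: "Six methamphetamine-related scenes in the extinction training session are based on these two rooms", and adds that they hold two or three times as many cues, put in other places.

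The Intervention section gives all four groups two sessions on consecutive days with the same extinction content. The R-10 min-E Group section sets out six extinction scenes of 5 min each, in random order. The end of the Introduction makes attenuation of renewal, relative to the other three interventions, part of the third objective. The document describes no methamphetamine scene that is held out of extinction.

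**The concern.** A renewal test needs a scene that extinction has not touched, because the question is whether responding returns once the person leaves the extinguished stimuli. Here the scene called novel appears to share its room with part of the extinction material. It has not been shown at pre-test or retrieval, but that is not the criterion in the Introduction.

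At stake is the renewal half of the third objective, which also appears in the abstract's aim and in the Discussion. Less renewal after retrieval-extinction can be shown only if extinction alone leaves some renewal to reduce. If the test room has been extinguished in every arm, including the extinction control, a null result may only mean that all arms were extinguished there. A positive result could not be attributed to renewal. No analysis can repair this once the data are collected.

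**Working it through.** **Step 1. Exposure of the two test rooms before and during testing** (VR Scenes and Videos; Intervention and its four group subsections).

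| Test scene | Pre-test | Retrieval | Extinction | Post-tests |
|---|---|---|---|---|
| Chosen room | shown | shown in R-10 min-E and R-6 h-E | versions with more cues, rearranged | all four |
| Other room ('novel') | not shown | not shown | versions with more cues, rearranged | all four |

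The extinction column is the same in both rows. The rooms differ only at pre-test and, in two arms, at retrieval. In NR-10 min-E the retrieval scene is neutral, and in RV-10 min-E it is a video, so in those arms the rooms differ at pre-test only. By the Introduction's criterion there is no ground for calling one a renewal scene and the other not.

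**Step 2. Extinction time.** Inputs: 6 scenes, 5 min per scene, 2 sessions.

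- Per session: 6 × 5 = 30 min. This reproduces the stated length of the extinction session.
- Total: 30 × 2 = 60 min per participant.

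**Step 3. Share in the 'novel' room.** Let k be the number of the six scenes built from that room. Exposure = k × 5 × 2 = 10k min. The document does not give k.

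- Even split (assumption), k = 3: 30 min.
- At least one scene from each room, k = 1 to 5: 10 to 50 min.
- k = 0 would remove the problem, but it means extinction in the chosen room only, which the text does not say.

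**Step 4. First exposure as a test scene.** The 'novel' room is shown at 1 day, 1 week, 1 month and 6 months. Only the 1-day test is its first showing as a test scene; by 6 months it has had three earlier showings.

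No figure in the document allows the loss of sensitivity to be quantified. The sample size calculation does not enter this point.

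**The case against.** **The extinction scenes are not the test scene.** They hold two or three times the cues in other positions, and the definition speaks of stimuli, not rooms. This is correct, and it means that direct extinction of the exact test layout is not established. It does not rescue the label, because the same is true of the chosen room used to assess spontaneous recovery.

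**The split may be individual.** The R-10 min-E Group section describes the six scenes as being in a room, and the equality of content is stated for groups, not for each participant. Extinction in the chosen room alone is therefore conceivable. The sentence that bases the six scenes on both rooms makes this the less likely reading. If it was intended, the text needs correcting all the same.

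**Three stronger readings are tempting but not supported.**

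- A reader might infer that the arm contrast loses its meaning. It does not: assignment is randomised and the extinction content is common to the groups, so prior extinction of the second room does not bias the comparison. What changes is the quantity estimated and, probably, the sensitivity.
- A reader might infer that the novel-scene response is set against a pre-test value that does not exist. The Study Procedure says that "a new VR session with novel methamphetamine-related cues will be added to the VR cue reactivity assessment during the four post-tests compared to pre-test". The natural meaning is that post-tests contain one session more than the pre-test did.
- A reader might infer that the lower familiarity of the unchosen room creates a spurious treatment effect. That would need the same pre-test comparison, and lower familiarity applies to every arm.

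**Repeated showing is deliberate.** The objectives ask how long any effect lasts, and the familiar scene is repeated too. This stands: repetition is not a fault, only something to state when reading the later visits.

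**Conclusion.** The point holds in a limited form. As written, the plan does not test renewal by its own definition. The 'novel' scene is new relative to pre-test and retrieval but, on the natural reading, not relative to extinction, and both test scenes stand in the same relation to extinction. The comparison between arms remains valid, but it estimates generalisation to a room not seen at pre-test or retrieval. Extinguishing that room in every arm probably reduces the chance of seeing an arm difference; this is a judgement, not a calculated loss.

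Exposure to versions of the 'novel' room is about 30 of 60 min under an even split, with a range of 10 to 50 min. This rests on each participant receiving scenes from both rooms, which is the likelier reading but is not stated outright. The first two objectives, the spontaneous-recovery assessment and the sample size are unaffected.

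**What to change.** Keep the renewal scene out of extinction, in one of two ways:

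1. Build the six extinction scenes only from the participant's chosen room, and say so. The other room is then new relative to extinction as well. The cost is that variants are needed for each room: if six distinct scenes per room are wanted, 6 × 2 = 12 in place of six. Extinction content would then depend on the room chosen, though by the same rule in every arm.
2. Add a third methamphetamine scene that appears in no pre-test, retrieval or extinction session, and validate it in the n = 10 panel already planned. The cost is one more scene to build.

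If neither is done, relabel the outcome as generalisation to a scene not seen at pre-test, and restrict the third-objective conclusion accordingly. That costs only wording, but it gives up the renewal claim.

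In all cases, state how the six extinction scenes divide between the rooms. Keep the scene at all four post-tests for the durability aim, and note that only the 1-day test is its first exposure as a test scene. Sample size and visit schedule stay as they are.

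### The room that serves as the novel scene for the renewal test also supplies scenes for extinction training, so its novelty relative to extinction is not secured

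*Protocol article*

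**What the plan says.** The Introduction describes extinguished responses that return "in the presence of drug-associated stimuli different from the ones used in extinction training (renewal", the last word being the protocol's label for the phenomenon. The reference point in that definition is the extinction material.

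The objectives, at the end of the Introduction, add a new scene at the follow-up tests "to assess if the effectiveness can translate to the new drug cue-induced craving and reactivity". Study Procedure likewise says that the added post-test scene contains novel drug cues.

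VR Scenes and Videos sets out what is available: "Two methamphetamine-related scenes are a living room and a bedroom with methamphetamine-related cues on a table or desk". One of the two is picked for each participant as the more familiar and is used at pre-test, at retrieval and at the post-tests. The other room, "which has not been chosen in the pre-test will be presented in four post-tests as a novel scene to test the renewal effect", is the renewal probe. The section then describes training: "Six methamphetamine-related scenes in the extinction training session are based on these two rooms", with two or three times as many cues, in different places.

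Under Intervention, training runs on two consecutive days, and "The content of the extinction training session will be the same for the four groups". The R-10 min-E Group section gives six scenes per session, each lasting 5 min.

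**The concern.** The definition asks whether responding returns to stimuli that extinction did not use. The probe is chosen by a different rule, namely that the room was not used at pre-test. Because the extinction scenes come from both rooms, a scene can satisfy the second rule and still fail the first.

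The renewal half of the third objective, the claim about transfer to new drug cues, and the renewal statements in Study Procedure and the Discussion all rest on this one scene. If participants respond weakly in it, two explanations compete: the effect reached untrained material, or that room was itself extinguished. The design as described cannot separate them. The problem is present at the 1-day post-test and does not depend on the scene being shown again at later visits.

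**Working it through.** **Inputs**
- Methamphetamine rooms: 2 (VR Scenes and Videos).
- Extinction scenes: 6, drawn from both rooms (VR Scenes and Videos). All 6 are shown in each session (R-10 min-E Group).
- Length of each scene: 5 min (R-10 min-E Group).
- Sessions: 2, on consecutive days, same extinction content in all arms (Intervention).
- First post-test: 1 day after the last session (Study Procedure).

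**Exposure before the first renewal test**

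Total extinction = 2 sessions × 6 scenes × 5 min = 60 min.

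If k of the 6 scenes come from the probe room, exposure there = 2 × k × 5 min = 10k min. The document does not give k. Using both rooms requires k from 1 to 5:

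| k | Minutes in variants of the probe room |
|---|---|
| 1 | 10 |
| 2 | 20 |
| 3 (even split, an assumption) | 30 |
| 4 | 40 |
| 5 | 50 |

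The firm result is that exposure is above zero for every k that uses both rooms. The conclusion does not need the even split.

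**What the probe room is new to**

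| Stage | Was the probe room used? |
|---|---|
| Pre-test | No |
| Retrieval, R-10 min-E and R-6 h-E | No, the other room is used |
| Retrieval, NR-10 min-E | No drug room is shown (neutral VR scene) |
| Retrieval, RV-10 min-E | No VR room is shown (video) |
| Extinction, all four arms, both days | Yes, in variants |

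The scene is therefore new relative to the pre-test and, where a VR drug room is shown at retrieval, new relative to retrieval. It is not shown to be new relative to extinction, which is the comparison in the Introduction's definition.

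**Sample size**

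The plan gives no exposure figure to reproduce. Its total sample size does reproduce: 4 × 20 = 80, and 80 / 0.85 = 94.1, rounded up to 95 as stated. This point does not change it.

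**The case against.** The best reply is that the definition speaks of stimuli, and Study Procedure of cues; neither speaks of rooms. The extinction scenes are only derived from the rooms, with two or three times the cues placed elsewhere, so the exact probe layout is not shown in training. That is fair as far as it goes. But the familiar test room stands in the same relation to its own extinction variants, so different placement gives the probe no special standing as a renewal test. Nor does the article say that the probe's cue items are kept out of the extinction scenes.

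One might also read the R-10 min-E Group section as placing all six scenes in a single room. VR Scenes and Videos says that they come from both.

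Several stronger readings are tempting, and the document does not support them:
- *That no post-test can measure renewal as defined, because the definition requires zero minutes in the room.* The Introduction sets no room-exposure criterion. What can be said is that novelty relative to extinction is not secured.
- *That training in the probe room is ten times the length of the test.* This needs an even split and a 3-min probe. Three minutes is given for the pre-test scenes; the length of the added post-test scene is not stated.
- *That the arm comparison in this scene is biased, or that generalisation is not tested at all.* Extinction content is the same in all arms, so the randomised comparison stays valid and still informs about carry-over beyond the room used at pre-test.
- *That an arm difference in renewal is diluted by a known amount.* Dilution is plausible, but its size cannot be obtained from the document.

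**Conclusion.** The point holds as a mismatch between the protocol's definition of renewal and the scene chosen to test it. Every participant has some of the 60 min of extinction in variants of the probe room before first being tested there: 10 to 50 min, assuming that each room supplies at least one of the six scenes.

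Consequences for interpretation:
- A low response in the probe scene may be direct extinction.
- No difference between arms says little about renewal.
- A difference between arms shows carry-over to a room not used at pre-test. It does not show renewal or response to new cues.

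The reach is limited. The first two objectives, the spontaneous-recovery half of the third, outcomes measured in the familiar room and the sample size are untouched. This should be fixed because it would otherwise support a wrong conclusion, but it does not threaten the trial's main comparison.

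**What to change.** The Introduction, Study Procedure and VR Scenes and Videos need to be reconciled before training starts, since exposure cannot be undone afterwards. There are two ways:

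1. **Reserve a scene.** Build one further methamphetamine scene whose room and cue items appear in no pre-test, retrieval or extinction scene, and use it for the renewal test. Add it to the planned validation in 10 people. Extinction content stays as it is. The cost is one more scene in the Unity environment already in use. A small drawback is that the new room may be less familiar to some participants, and the Discussion already warns that unfamiliar scenes may draw responses to things other than the drug cues.

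2. **Relabel.** Describe the current measure as the response in a room not used at pre-test but used in extinction. Remove the renewal and new-cue claims from the third objective, from the related statements in Study Procedure and the Discussion, and from the conclusions. The cost is a wording amendment.

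The first keeps the scientific question; the second gives it up. Neither adds participants or visits.
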